**Measurements**

For all measurements, patients will be instructed to eat a light meal 2 h beforehand, to avoid caffeinated beverages on the experimental days, and do not perform exercise in the previous 48 hours.

**Primary outcome**

**Ambulatory blood pressure**

Ambulatory BP will be assessed by an oscillometric device (Dyna-MAPA, Cardios, Brasil) programmed to take measurements every 15 min for 24 hours. The recordings will only be accepted if at least 80% of the readings were successfully performed. Patients will be instructed to complete a diary to record the time of sleep, waking and daytime activities. Ambulatory data will be analysed using the averages of 24 h, awake and asleep periods [5].

**Secondary outcomes**

**Cardiovascular Function**

**Office blood pressure**

Systolic and diastolic office BP will be measured by an automatic monitor (HEM-742, Omron Healthcare, Japan). Patients will be resting for ten minutes in a supine position. Three consecutive measurements will be performed with one-minute interval between them, in both arms, and with the appropriate size cuff. The value used will be the average of the last two measures.

**Central blood pressure**

Central BP will be obtained by the pulse wave analysis recorded in the left radial artery using applanation tonometry (SphygmoCor AtcorMedical, Sydney, Australia) and a validated transfer function algorithm provided by the Sphygmocor® software will estimate the central values of systolic, diastolic, and mean BP [6].

**Heart rate variability**

Heart rate variability will be assessed from the beat to beat intervals obtained by a heart rate monitor (V800, Polar Electro, Finland) during 10 min with patient in supine position. Continuous stationary data recorded for at least 5 min will be used for analysis. All analyses will be performed using a software (Kubios HRV, Biosignal Analysis and Medical Imaging Group, Finland) according to the recommendations of the Task Force for heart rate variability [7]. The time-domain parameters (SDNN – standard deviation of all RR intervals, RMSSD – root mean square of the squared differences between adjacent normal RR intervals, pNN50 – the percentage of adjacent intervals over 50ms) and frequency-domain (low frequency, high frequency, and low frequency/high frequency) parameters will be analyzed as previously described [7].

**Arterial stiffness**

The arterial stiffness parameters, such as pulse pressure (difference between systolic and diastolic blood pressure) and augmentation index (the proportion of pulse pressure that is attributed to the reflected pulse wave) will be obtained through applanation tonometry (SphygmoCor, AtCor Medical, Australia), in radial artery. Carotid-femoral pulse wave velocity will be measured by applanation tonometry (Sphygmocor, AtCor Medical, Australia) following the guidelines of the Clinical Application of Arterial Stiffness, Task Force III [6]. Distance between carotid artery to the suprasternal notch and femoral artery to the suprasternal notch will be measured using a standard tape. Electrocardiogram will be simultaneous assessed to obtain heart rate and, according to a “foot-to-foot” method, the time difference between the points will be measured. Then, the distance between the two arteries will be divided by the time difference.

**Vascular function**

Vascular function will be estimated by resting blood flow and flow-mediated dilation measurements obtained by ultrasound technique according to recent recommendations [8]. Images of the brachial arteries will be recorded by a two-dimensional ultrasound with spectral Doppler and linear transducer (Ultra-0122, Philips, The Netherlands). For that, each patient will stay in supine position for at least 20 minutes. After location of the arteries, the transducer will be placed and to attest to the good quality of the arterial pulse obtained, the Doppler sound will be activated.

The contrast resolution, depth, and gain will be adjusted to optimize the longitudinal images of the lumen/arterial wall interface. Insonation angle-corrected at 60°, blood velocity spectra will be simultaneously recorded via the pulsed-wave mode at linear frequencies of 13 and 6.0 MHz, respectively.

Baseline diameter and blood velocity waveforms will be continuously recorded over 120 s. After that, a cuff, placed distal to the image capture, will be inflated with a pressure above 50 mm Hg of the systolic BP measured before the examination. The occlusion will be maintained for five minutes, and, after this period, rapidly released. The image and Doppler captures recordings will be resumed 30 s before deflation and will maintain for 180s after.

The diameters and post-occlusion blood flow velocities will be measured after the release. The vasodilatory capacity will be calculated by the flow-mediated dilation, the percentage of increase in diameter of the brachial artery post occlusion compared to their baseline values.

**Functional Capacity**

**Six-minute walk test**

The six-minute walking test will be performed along a 30-meter-long corridor, as previously described [9,10]. Briefly, patients will be encouraged to “walk at their usual pace for six-minutes and cover as much ground as possible” and rest if necessary. The outcomes will be the onset claudication distance (distance walked when the patients related the occurrence of symptom of intermittent claudication) and six-minute total walking distance (maximum distance achieved by the patient at the end of the test).

**Two-minute step test**

The 2 two-minutes step test will be performed as previously described [11]. Patients will be required to march in place for 2 minutes, being counted the maximum number of steps. The march will be consisted of alternating elevation of the knees to the mean height of the thigh (midpoint between the patella and the anterior superior iliac spine). Patients will be instructed to complete as many steps as possible during the test.

**Walking impairment questionnaire**

The walking impairment questionnaire [12] contains three domains measuring three factors of walking impairment: walking distance, walking speed, and the ability to climb stairs. Patients will be asked how difficult it was to walk in these situations and should answer as “none, slight, some, much or unable”. Each domain is scored on a 0 to 100 scale, where 0 represents extreme limitation and 100 represents no walking long distances difficulties, walking rapidly, or climbing 3 stair flights, respectively.

**Walking estimated limitation calculated by history**

The walking estimated-limitation calculated by history is a four-question questionnaire which the first 3 are related to how long patients can perform the task easily on levels ground and without stopping in different walking speed and the last one is related to speed comparison with their relatives, friends or people at same age. The score (ranges from 0 to 100) is calculated as the sum of the values for the first three, minus one, multiplied by the coefficient for the final (walking speed) questionnaire item [13].

**Handgrip test**

The handgrip test will be performed to evaluate the handgrip strength. The test will be performed using a dynamometer with digital display (EH101, Camry, USA), following the previously protocol [14] that will be calibrated with a scale from 0 to 100 kgf. Patients will be evaluated seated with slightly adducted shoulder, elbow flexed at 90°, forearm and wrist in neutral position. The test will be performed in three attempts in each of the dominant and non-dominant hands, alternately, and the highest value will be used for analysis.

**Baltimore Activity Scale for Intermittent Claudication**

The Baltimore Activity Scale for Intermittent Claudication will be obtained following the previously protocol [15]. It consists of five questions related to the symptoms of intermittent claudication. For each question, patient selects the answer that best describes their symptoms and the level of physical activity. Values range from 0 to 2 points, and the total score is the sum of the points from the 5 questions. The score ranges from 0 to 10, with zero being the lowest levels of physical activity and ten being the highest [15].

**Short Physical Performance Battery**

Functional capacity will also be obtained by the short physical performance battery as previously described [16]. The short physical performance battery is a group of measures that combines the results of gait speed, chair stand, and balance tests. The total score will be calculated from the performance in the three tests, ranging from 0 to 12, with 0 as worst function and 12 as best function.

**Cognition**

Standardized cognitive tasks to quantify executive function and memory will be evaluated as previously described [17]. These assessments will be carried out on paper and include: a) executive function - Test A and B, coding of digit symbols; b) memory: Hopkins verbal learning test (immediate and delayed recovery), forward and backward digit range; c) verbal fluency: task of generating words ("S" and animals).

**Quality of life**

**Vascular quality of life questionnaire - 6**

The quality of life will be evaluated by the vascular quality of life questionnaire VascuQoL-6, as previously described [18]. The questionnaire is composed by six items evaluating the impact of disease on social aspects and capacity to perform daily activities. Each item is scored 1-4. The total score is achieved by summarizing the score on each item, resulting in a score between 6 and 24. Higher value indicates better health status.

**World Health Organization Quality of Life (WHOQOL) brief**

The WHOQOL-brief instrument encircles different aspects of physical and mental health, which encircle the follow dimensions: general health status, functional capacity, physical aspects, pain, vitality, mental health, emotional aspects and social aspects of life. Each answer receives a score, which is added to a constant to determine the different components of quality of life [19].

**Intervening variables**

In order to minimize the possible influences of intervening variables, and to ensure that the changes generated on outcomes will be caused by ACT or WT interventions, medications, dietary pattern, and physical activity levels will be monitored.

To control of medication, each week the researcher will be responsible for filling a container with the medications prescribed for the patient, according to the frequency, time and recommended dosage. At the end of the week (in the second weekly session), the researcher will check if the patient correctly took the medications. Patients will be followed during the 12 weeks period of intervention.

For food monitoring, before and after the intervention period, patient will be asked to fill a food diary for four days of the week, including at least one day of the weekend. Based on this information, it will be possible to analyze changes in the dietary pattern of the patients, as well as to estimate the caloric intake ingested before and after the intervention period.

Finally, patients will use a smartwatch (A300, Polar, Finland) that will estimate their physical activity levels. The POLAR A300 is a monitor coupled with a 3D accelerometer that records patient’s movements. Through it, it is possible to analyze the frequency, intensity and regularity of the movements and, consequently, to determine the physical activity levels. Patients will use this monitor for one week before the first evaluation and after the last week of training, allowing to identify possible changes in physical activity level with ACT, WT and CG interventions.

**Statistical analysis**

**Power and sample size**

The sample size was determined by the a priori specific sample calculation for clinical trials involving parallel groups, in this case two-way ANOVA with repeated measures. Using GPower 3.1.9.2 software it was considered an effect size of 0.25; α of 0.05; power (1 - β) of 0.80; correlation coefficient between repeated measures of 0.6; non-spherical correction (ɛ) of 1 and three groups two measures. Thus, the minimum total size reached 36 subjects (12 per group) with 83% power. Considering the possibility of sample loss, the sample was inflated by 20%, resulting in a sample of 45 patients (15 per group).

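### Free improvement: sizing on a repeated-measures ANOVA leaves the baseline unadjusted; adjustment would lift power at 36 evaluable patients from about 83% to about 89–90%

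*Protocol*

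**What the plan says.** The Power and sample size section of the protocol says that the calculation is for parallel groups, "in this case two-way ANOVA with repeated measures". Its inputs are: "it was considered an effect size of 0.25", α of 0.05, "power (1 - β) of 0.80", "correlation coefficient between repeated measures of 0.6", sphericity assumed, and "three groups two measures". The result is that "the minimum total size reached 36 subjects (12 per group) with 83% power", raised to 45 (15 per group) to allow for 20% loss.

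The primary outcome is ambulatory blood pressure. Under Study design, the cardiovascular assessments are made before allocation and patients are assessed again after 12 weeks. The protocol names no other analysis method and does not mention adjustment for baseline.

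**The concern.** With one baseline and one follow-up value, the interaction test of a repeated-measures ANOVA uses only each patient's change. Subtracting the whole baseline amounts to fixing its coefficient at 1. When the correlation between visits is 0.6 and the variances are equal, the best linear coefficient is 0.6, so the change score over-corrects. The excess appears as extra error variance. It also carries part of any chance baseline difference between arms into the estimated effect.

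What is at stake is precision in a trial with 12 to 15 patients per arm. The baseline value is collected before randomisation in any case, so using it as a covariate costs nothing.

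**Working it through.** **Inputs**, all from Power and sample size: f = 0.25, α = 0.05, ρ = 0.6, k = 3 groups, m = 2 measures, N = 36.

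**1. Reproduce the protocol's figure.** For the group-by-time interaction:

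λ = f² × N × m / (1 − ρ) = 0.0625 × 36 × 2 / 0.4 = 11.25, with 2 and 33 degrees of freedom. Power = 82.6%, which is the stated 83%.

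N = 33 gives 78.6%, so 36 is the smallest total with equal groups that reaches 80%. The enrolment figure is 36 / 0.8 = 45, also as stated. The other usual settings do not reproduce 83%: the between-groups test gives 28%, the time effect 90%, and the alternative effect-size definitions 21–23%. The interaction is therefore the test on which the trial was sized.

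**2. Error variance per patient** (equal variance σ² at both visits):

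- Change score: 2(1 − ρ)σ² = 2 × 0.4σ² = 0.80σ²
- Baseline-adjusted 12-week value: (1 − ρ²)σ² = (1 − 0.36)σ² = 0.64σ²
- Ratio: 0.64 / 0.80 = 0.80, or in general (1 + ρ)/2

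The gap, 0.80 − 0.64 = 0.16 = (1 − ρ)², is the baseline variation that the change score leaves in.

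**3. Power with baseline adjustment, same group differences.** On this effect-size scale, the variance of the group mean changes is 4f²σ², so

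λ = 4 × f² × N / (1 − ρ²) = 4 × 0.0625 × 36 / 0.64 = 14.06, with 2 and 32 degrees of freedom. Power = 90.3%.

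Simulation of 20,000 trials for each of two patterns of group means gave 89.2% and 89.7% for ANCOVA, and 82.4% and 82.7% for the ANOVA. The formula is slightly optimistic for ANCOVA at this size, so about 89–90% is a fair statement.

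**4. Other sizes, by formula, at ρ = 0.6.**

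| Evaluable N | Repeated-measures ANOVA | Baseline-adjusted |
| --- | --- | --- |
| 30 | 73.9% | 83.2% |
| 36 | 82.6% | 90.3% |
| 45 | 91.0% | 96.0% |

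**5. Dependence on the correlation**, N = 36, f held at 0.25, by formula.

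| ρ | Repeated-measures ANOVA | Baseline-adjusted |
| --- | --- | --- |
| 0.4 | 64% | 80% |
| 0.5 | 73% | 85% |
| 0.6 | 83% | 90% |
| 0.7 | 92% | 96% |
| 0.8 | 98.7% | 99.3% |

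**6. Chance imbalance.** With 12 per arm, the standard deviation of the baseline difference between two arms is √(2/12)σ = 0.41σ. A change-score comparison carries (1 − ρ) = 40% of that difference into the estimate, typically 0.4 × 0.41σ = 0.16σ. This is the same loss as in step 2, seen from the side of the estimate, and is not an additional one.

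**The case against.** The strongest reply is that nothing in the protocol is wrong. The calculation reproduces, it meets its 80% target, and the allowance for losses is applied correctly. Change-score analysis is unbiased under randomisation; imbalance in a given sample is noise, not bias. All of this stands. A reader might infer that the trial is underpowered or its test invalid, and the documents support neither.

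Second, the ANOVA is named only as the basis of the sample size. No sentence declares it the primary analysis, and a statistical analysis plan that is not shown may already adjust for baseline. This also stands as a limit. Reading the ANOVA as the intended analysis is reasonable, since it is the only method named, but it is an inference.

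Third, the gain depends on an assumed correlation of 0.6. It shrinks to about 4 points at 0.7 and under 1 point at 0.8. It grows as the correlation falls, which is where the ANOVA drops below its target. Adjustment has the higher computed power at every value tabulated.

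A stronger reading is also tempting. Under Ambulatory blood pressure, "The recordings will only be accepted if at least 80% of the readings were successfully performed", and a classical repeated-measures ANOVA needs both values, so one might conclude that the protocol drops every patient with one rejected recording. It does not say so. It is silent on whether such a recording is repeated, imputed or excluded, and a rejected baseline recording could be repeated before allocation. It gives no rejection rate, so no loss of power can be computed from it, and the 20% allowance may already cover unusable recordings. Nor would plain ANCOVA cure the problem, because it needs both recordings too.

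**Conclusion.** The point holds as an efficiency improvement, not as an error. On the protocol's own inputs, adjusting for baseline cuts the error variance by 20%. It raises power at 36 evaluable patients from about 83% to about 89–90%, or gives 83% with 30 evaluable patients.

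The size of the gain rests on ρ = 0.6, equal variances at the two visits, equal expected baselines under randomisation, and complete data on the 36. It concerns the method the protocol names. If the analysis plan already specifies baseline adjustment, what remains is to bring the protocol's wording into line with it.

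**What to change.** - Name the primary analysis in the Statistical analysis section: ANCOVA of 12-week ambulatory blood pressure on arm and baseline ambulatory blood pressure.
- If patients with only one accepted recording are to be kept, specify instead a likelihood-based mixed model with a common baseline mean across arms. Once recordings are missing, the two models use different patients, so the protocol should state which one is primary.
- Report between-arm differences with 95% confidence intervals.
- Use the same model for the continuous secondary outcomes.
- Keep 36 evaluable and 45 enrolled, and add a sentence that the figure is conservative because it takes no credit for baseline adjustment.

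The cost is analysis wording only: no added patients, visits or procedures. The change should be made before any outcome data are examined by arm.
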